## Abstract

**Background:**

Cerebrovascular reactivity (CVR) is the change in cerebral blood flow in response to a vaso-active stimulus, and may assist the treatment strategy of ischemic stroke. However, previous studies reported that a therapeutic strategy for stroke mainly depends on the degree of vascular stenosis with steady-state vascular parameters (e.g., cerebral blood flow and CVR). Hence, measurement of CVR by multimodal imaging techniques may improve the treatment of ischemic stroke.

**Methods/design:**

This is a prospective, randomized, controlled clinical trial that aimed to examine the capability of multimodal imaging techniques for the evaluation of CVR to improve treatment of patients with ischemic stroke. A total of 66 eligible patients will be recruited from Renji Hospital, Shanghai Jiaotong University School of Medicine. The patients will be categorized based on CVR into two subgroups as follows: CVR > 10% group and CVR < 10% group. The patients will be randomly assigned to medical management, percutaneous transluminal angioplasty and stenting, and intracranial and extra-cranial bypass groups in a 1:1:1 ratio. The primary endpoint is all adverse events and ipsilateral stroke recurrence at 6, 12, and 24 months after management. The secondary outcomes include the CVR, the National Institute of Health stroke scale and the Modified Rankin Scale at 6, 12, and 24 months.

**Discussion:**

Measurement of cerebrovascular reserve by multimodal image is recommended by most recent studies to guide the treatment of ischemic stroke, and thus its efficacy and evaluation accuracy need to be established in randomized controlled settings. This prospective, parallel, randomized, controlled registry study, together with other ongoing studies, should present more evidence for optimal individualized accurate treatment of ischemic stroke.

**Trial registration:**

Chinese Clinical Trial Registry, ID: ChiCTR-IOR-16009635; Registered on 16 October 2016.

All items are from the World Health Organization Trial Registration Data Set and registration in the Chinese Clinical Trial Registry: ChiCTR-IOR-16009635.

## Introduction

Stroke is the second most common cause of death and the major cause of disability worldwide after ischemic heart disease, especially in developing countries [1]. Ischemic stroke occurs when a blood vessel supplying blood to a part of the brain is obstructed, and it accounts for about 87% of all strokes. A remarkable risk of recurrent ischemic stroke was reported in patients with symptomatic, major cerebral arterial occlusion or stenosis [2]. Therefore, an effective therapeutic approach for intracranial arterial stenosis is urgently required.

The treatment of ischemic stroke has been investigated by a number of high-quality trials: The Japanese extracranial-intracranial bypass (EC-IC) bypass trial (JET2) study revealed that compared with the medical arm of the Japanese EC-IC bypass trial (JET) study including patients with cerebral blood flow (CBF) < 80% and cerebrovascular reactivity (CVR) < 10% as a historical control, the incidence of ipsilateral stroke recurrence was significantly lower in the JET2 study, demonstrating that EC-IC bypass surgery is unlikely to benefit patients with CBF > 80% or CVR > 10% [3]. Another recent trial involving aggressive medical treatment with or without stenting in high-risk patients with intracranial arterial stenosis (SAMMPRIS), demonstrated the use of aggressive medical management rather than percutaneous transluminal angioplasty and stenting (PTAS) with the Wingspan system in high-risk patients with atherosclerotic intracranial arterial stenosis [4]. AL Hasan conducted a trial for treating ischemic stroke, and showed a 14.7% risk of stroke or death in the stenting group versus 5.8% in the medical group at 30 days, and 23% in the stenting group versus 15% in the medical group at a median follow-up of 32.4 months. However, the treatment strategy of intracranial arterial stenosis or occlusion mainly depends on the degree of vascular stenosis, with or without consideration of hemodynamic factors at the distal end-to-side anastomosis of a bypass graft and CVR factors, or steady-state vascular parameters, such as CBF and cerebral blood volume (CBV). Hence, we present a study protocol for the measurement of CVR using multimodal imaging data for cerebral arterial occlusion or stenosis patients.

The CVR is the ability of cerebral vessels to dilate or constrict in response to challenges or maneuvers [5, 6]. In addition, CVR is thought to be an important index of the brain’s vascular health, and provides vascular-reserve information that is complementary to steady-state vascular parameters, including CBF and CBV [7, 8]. There have been two main approaches to measuring CVR. One approach attempts direct CBF measurements of the brain tissue with flow-sensitive imaging techniques such as positron-emission tomography (PET), nuclear medicine (NM) techniques, computed tomography (CT) perfusion, or magnetic resonance imaging (MRI) perfusion before and after a vasodilatory stimulus. The second approach involves transcranial Doppler (TCD) measurement of flow velocities (typically in the middle cerebral artery (MCA)) distal to a lesion both before and after a vasodilatory stimulus, with the increase flow velocity considered a surrogate for CVR [9–12]. We intend to precisely evaluate the change of CVR before and after surgical or medical treatments by multimodal image including MRI, CT, and single-photon-emission computed tomography (SPECT), so that we can make strategies for individualized accurate diagnosis and treatment for the ischemic stroke [3, 13].

Due to the lack of effective therapeutic approaches for intracranial arterial stenosis or occlusion, the present trial was registered at the Chinese Clinical Trial Registry database, and approved by the Center for Reproductive Medicine at Renji Hospital (Shanghai, China). The present trial was designed to determine whether multimodal imaging data can effectively enhance the treatment strategy for adult patients with intracranial arterial stenosis or occlusion.

## Methods/design

### Study design

This prospective, randomized, controlled clinical trial aimed to examine the efficacy of multimodal image data based on CVR to treat ischemic stroke. A total of 66 patients, who met the inclusion criteria, were admitted to Center for Reproductive Medicine at Renji Hospital, Shanghai Jiaotong University School of Medicine (Shanghai, China). The eligible patients were categorized based on CVR into two groups as follows: CVR > 10% group and CVR < 10% group. In addition, these two groups were randomly assigned to the groups of medical management, single angioplasty, PTAS, and IC-EC bypass in a 1:1:1 ratio. Fig. 1 shows the study flowchart of our trials.

**Fig. 1 Fig1:**
[figure not shown]
Study flowchart of our trial

### Inclusion and exclusion criteria

The eligible patients were identified if they met the following criteria: (1) clinical requirements: (a) men and women aged between 18 and 70 years, (b) independency in the activities of daily living (modified Rankin scale score of 0–2) on admission or after resuscitation; (2) radiological requirements: (a) occlusion or severe stenosis in the main trunk of the MCA or the supraclinoid segment of the internal carotid artery, (b) CT and MRI: no large infarction and no contrast enhancement in the infarcted area; and (3) signing the written informed consent form.

Exclusion criteria were as follow: (1) no independency in the activities of daily living (modified Rankin scale score of 3–5); (2) occlusive lesions of the cerebral arteries due to diseases other than atherosclerosis; (3) malignant tumors or multi-organ dysfunction involving the heart, liver, kidney, or lung; (4) myocardial infarction within the past 6 months; (5) uncontrolled diabetes showing a serum fasting blood glucose level of > 300 mg/dL, or requiring insulin; (6) hypertension with a diastolic blood pressure of > 110 mmHg;7; (7) artery-to-artery embolism; and (8) cardioembolism.

### Ethical approval and consent to participate

The study protocol was approved by the Ethics Committee of Renji Hospital. Furthermore, the present trial was registered at the Chinese Clinical Trial Registry (Registration No. ChiCTR-IOR-16009635). The trial was performed in accordance with the Declaration of Helsinki. All the participants signed the written informed consent form prior to start of study. The principal investigator explained the content of the research plan with the patient; including whether they agree to use of their data and asked for permission for the research team to share their relevant data with people from the universities taking part in the research or from the regulatory authorities. The principal investigator will obtain informed consent or assent from potential trial participants or the patient’s legal representative [14].

### Randomization and allocation concealment

In this trial, randomization sequence was generated by an independent institution that was not involved in the determination of eligibility.

### Treatment protocol

The eligible patients underwent multimodal imagine to measure CVR. Regional CBF was quantitatively measured more than 3 weeks after the last ischemic attacks using computed tomography perfusion (CTP) or SPECT (123I-IMP). A study of a small number of patients with chronic arterial stenosis compared ASL perfusion with ACZ challenge with iodine 123 *N*-isopropyl-piodoamphetamine (123I-IMP) SPECT, and the fixed concentration of CO_2_ was provided by a gas-delivery system using a pressure transmitter to control the gas blender with prospective gas-targeting algorithms. Subjects underwent SPECT/CTP scanning, and were asked to breathe normally for 10 min. The region of interest (ROI) was designated manually in the cerebral cortex in the territory of the ipsilateral MCA at the level of the anterior horn of the lateral ventricle. ROIs were also placed in the bilateral cerebellar hemispheres and in the contralateral MCA territory as reference. Regional CBF was expressed as relative values (%) to normal control values of each institute obtained from volunteers free of cerebrovascular disease. CVR was calculated as follows:
$$ CVR\ \left(\%\right)=\left[\left({CO}_2\  challenge\  CBF- rest\  CBF\right)/ rest\  CBF\right]\times 100. $$

All treatment procedures and specific operating protocols for the management of ischemic stroke in our trial were standardized based on current guidelines.

Surgical intervention was microsurgical end-to-side anastomosis of a superficial temporal artery branch to a cortical branch of the MCA. If the superficial temporal branch was felt to be inappropriate, the occipital artery could be used. For participants in the surgical group, preoperative and postoperative antithrombotic treatments were carried out by a neurosurgeon. Patients in the PTAS group received stenting when “alarm” symptoms were relieved after MT. Participants in the nonsurgical group continued to receive the antithrombotic treatment preferred by their physicians. Targets for controlling risk factor were 130/85 mmHg for blood pressure, 100 mg/dL for low-density lipoprotein, 150 mg/dL for triglycerides, and 7% for hemoglobin A1C.

### Study endpoints

Each patient was followed-up for 2 years by a neurologist and a neurosurgeon in each participating institute. Primary and secondary endpoints were defined as all adverse events and ipsilateral stroke recurrence at 6, 12, and 24 months after management, respectively. Neurological findings, intracranial CT/MRI, and CBF/CVR measurements were examined and reported at the time of enrollment and at 6 months, 1 year, and 2 years after enrollment. Evaluation of cognitive function and angiography were carried out at the time of enrollment and 2 years after enrollment. The functional outcomes were measured using CVR, the National Institute of Health stroke scale (NIHSS), and the Modified Rankin Scale (MRS) at 6, 12, and 24 months after the management.

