### Sample size and data analysis

The number of patients included in the registry was equal to 60, and this trial involved 66 eligible ischemic-stroke patients, in which about 10% of patients were lost to follow-up. Data were presented as mean ± standard deviation (SD) for continuous variables, and as frequency for categorical variables. Significances between variables were analyzed using the chi-square test. Associations between clinical variables and outcomes were analyzed, and predictors of long-term outcome were identified using univariate and multivariate regression analyses. The difference was expressed as an odds ratio (OR, with 95% confidence interval (CI)), and *P* < 0.05 was considered statistically significant.

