Finally, we recorded all the data related to the changes of CVR before and after treatment by multimodal imaging. The adverse events during the follow-up period were also taken and divided into ipsilateral stroke recurrence and all adverse events. We consequently found that such data could be help to analyze the effects of relevant confounding factors.

Our trial also indicated whether CVR can effectively and safely help improve the outcome in patients with intracranial arterial stenosis or occlusion. Regarding the major challenges in performing a clinical trial on ischemic stroke, the necessity for huge amounts of data is inevitable.

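### The Abstract and the Methods define the primary endpoint in two incompatible ways, and neither names a lead time point

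*Protocol article*

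**What the plan says.** The protocol article ranks its endpoints in two places.

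- **Abstract, Methods/design:** "The primary endpoint is all adverse events and ipsilateral stroke recurrence at 6, 12, and 24 months after management". It continues: "The secondary outcomes include the CVR, the National Institute of Health stroke scale and the Modified Rankin Scale at 6, 12, and 24 months".
- **Methods, Study endpoints:** "Primary and secondary endpoints were defined as all adverse events and ipsilateral stroke recurrence at 6, 12, and 24 months after management, respectively". The cerebrovascular reactivity (CVR), NIHSS and Rankin measures are described there without the label secondary: "The functional outcomes were measured using CVR, the National Institute of Health stroke scale (NIHSS), and the Modified Rankin Scale (MRS").

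The Discussion mentions the events once more, saying they were "divided into ipsilateral stroke recurrence and all adverse events", without ranking them. Sample size and data analysis gives one general test ("Significances between variables were analyzed using the chi-square test"), regression with odds ratios, and one threshold ("0.05 was considered statistically significant"). It links the sample size of 60, raised to 66, to no endpoint.

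**The concern.** Stroke recurrence cannot be part of the primary endpoint and also be secondary. If one endpoint shows a difference between arms and the other does not, the trial is positive under one sentence and negative under the other. The choice of time adds a second degree of freedom, since three times are listed and none leads.

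The Methods version also fits the trial's question poorly. The Discussion says that the study explores recurrence of ischemic stroke after treatment. The Introduction builds its case on ipsilateral stroke recurrence and on stroke or death. A primary endpoint of all adverse events does not directly answer that question. It pools recurrent stroke with complications of stenting or bypass, which only the arms assigned to a procedure can have. Under the Abstract version the two endpoints overlap, because a recurrent ipsilateral stroke is itself an adverse event.

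The Follow-up section gives the Institutional Review Board access to interim results. An ambiguity settled late could therefore be settled with results in view, or appear to have been.

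**Working it through.** **Step 1: the two definitions side by side.**

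| Item | Abstract | Study endpoints |
|---|---|---|
| All adverse events | primary | primary |
| Ipsilateral stroke recurrence | primary | secondary |
| CVR, NIHSS, Rankin | secondary | functional outcomes, unranked |
| Times | 6, 12, 24 months | 6, 12, 24 months |
| Lead time | none named | none named |
| Co-primary or composite | not stated | does not arise |

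The second row is the contradiction. The word 'respectively' pairs two labels with two endpoints in order. It may be a slip, perhaps meant for the time points, but as written it ranks the endpoints.

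**Step 2: does anything else resolve it?** The Discussion lists both event categories without rank. The only checkable sample-size figure is the inflation for loss: 60 × 1.10 = 66 (60/0.90 = 66.7, so 67, would be the stricter form). That reproduces the article's figure but says nothing about the endpoint, because no event rate, effect size or power is attached to the 60.

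**Step 3: what the open choice could cost (illustration only).** From the article: three arms at 1:1:1, so 66/3 = 22 or 60/3 = 20 per arm; chi-square test; threshold 0.05; three times.

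Upper bounds, if the tests were independent, from 1 − 0.95^k:

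- one endpoint at three times, k = 3: 1 − 0.95³ = 14.3%
- two endpoints at three times, k = 6: 1 − 0.95⁶ = 26.5%

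Events counted cumulatively at 6, 12 and 24 months are positively correlated, so the true figures are lower. They were simulated with no difference between arms (100,000 trials per scenario, 20 or 22 per arm). The assumed rates are:

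- cumulative stroke risk of 6/10/15% or 10/15/23% at the three times;
- other adverse events from 15/20/25% up to 30/40/50%;
- all adverse events defined as either kind.

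| Assumed test structure, each test at 0.05 | One endpoint | Both endpoints |
|---|---|---|
| One three-arm chi-square per time | 9–11% | 17–19% |
| All three pairwise contrasts per time | 18–24% | 35–39% |

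The largest figure needs 2 endpoints × 3 times × 3 contrasts = 18 tests. One endpoint with pairwise contrasts needs 9.

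**Step 4: after correction.** One endpoint, one time and one three-arm test gives the nominal 5%. For stroke at 24 months the simulation gave 4.4–5.2%.

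**The case against.** The best reply is that the contradiction is a wording slip, and that the rest is inference from a condensed article whose statistical analysis plan is not shown. Much of that stands, and it limits the point in four ways.

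- **Multiplicity.** A reader might infer that each time point and each pair of arms is tested separately at 0.05, giving 18 tests and a false-positive chance near 40%. The article does not say so. It names a chi-square test and a general threshold, which fit a single three-arm test equally well, and a multiplicity rule may sit in the analysis plan. The 18-test count also fits only the Abstract version read as two either-or co-primaries; under the Methods version there is one primary endpoint. Absence of an adjustment is therefore not a finding here.
- **Bias.** A reader might infer that counting all adverse events is biased toward the medical arm. That goes too far. Procedural complications are real consequences of being assigned to a procedure, and medical patients have adverse events too. The fair criticism is that this endpoint answers a different question. How adverse events are graded may be left to the full protocol.
- **Choice of primary.** The documents require reconciliation; they do not dictate the answer. Ipsilateral stroke alone leaves out death and stroke elsewhere. It is also a weak endpoint at this size. With 20–22 per arm, a global chi-square test has about 9% power at assumed risks of 15/23/15%, and about 26–29% at 15/23/5%.
- **Clock.** Both sentences count time from management. Moving the start to randomisation would be a separate change needing its own argument, and it is not part of this point.

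None of this removes the contradiction. Both sentences are complete and state the endpoint outright. An analysis plan should implement the protocol's primary endpoint, not choose between two.

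**Conclusion.** The point holds as a contradiction in the primary endpoint, together with the absence of a lead time. It rests on the text alone and needs no assumption. It should be corrected before any results by arm are examined, because the trial's conclusion can turn on it.

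The false-positive figures (9–11% for one endpoint with one three-arm test per time, up to 35–39% for both endpoints with all pairwise contrasts) only show what the open choice could cost. They depend on assumed event rates, on three arms of 20–22, and on a test structure that the article does not state. They are not a measured error rate of this trial.

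**What to change.** 1. Reconcile the Abstract and Study endpoints, naming the same single primary endpoint at one time point in both. Ipsilateral stroke recurrence by 24 months is the option closest to the stated question. All adverse events then become the safety outcome, and 6 and 12 months are supportive. If the investigators prefer another primary, including both components, they should say whether it is a composite or a pair of co-primaries.
2. Give CVR, NIHSS and the Rankin scale the same rank in both places.
3. Compare the three arms on the primary with one global test at 5%, and read the pairwise contrasts only if it is significant. For three arms this is a closed procedure and needs no further split of the 5%.
4. Trial status gives a start date of 6 June 2018, so make the change as a dated, justified amendment decided by people without knowledge of results by arm, and update the registry entry.

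**Cost.** No new data are needed, but this is a formal mid-trial amendment and more than an edit. The 6- and 12-month results lose confirmatory status. The low power shown above remains, and the report should acknowledge it.

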### Data collection

The baseline data were collected including the following variables: hypertension, smoking status and whether diabetic, clinical presentation (i.e., initial ischemic stroke, on admission and before treatment); neurological functions (NIHSS and MRS), vascular stenosis, timing of management, treatment procedure, neurological conditions within 72 h after treatment, complications during hospitalization, follow-up, and presumed reasons of death. There is no storage of biological specimens for genetic or molecular analysis in the current trial and for future use in ancillary studies.

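### The only stroke-specific endpoint omits non-ipsilateral strokes, and deaths not due to ipsilateral stroke, around a procedure; a stroke-or-death composite, identical in all arms, should replace it

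*Protocol article*

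**What the plan says.** The one stroke-specific endpoint, in Study endpoints, is "ipsilateral stroke recurrence at 6, 12, and 24 months after management".

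The full sentence there is: "Primary and secondary endpoints were defined as all adverse events and ipsilateral stroke recurrence at 6, 12, and 24 months after management, respectively". Read with its last word, this makes all adverse events primary and ipsilateral recurrence secondary.

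Abstract, Methods/design: "The primary endpoint is all adverse events and ipsilateral stroke recurrence at 6, 12, and 24 months after management". Here both are primary, and the secondary outcomes are CVR, NIHSS and modified Rankin Scale.

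Discussion, on how events are classed: "The adverse events during the follow-up period were also taken and divided into ipsilateral stroke recurrence and all adverse events". No third class, such as any stroke or death, is named.

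Timing: endpoints run from management, whereas neurological findings, imaging and CVR are "examined and reported at the time of enrollment and at 6 months, 1 year, and 2 years after enrollment". No 30-day outcome is named.

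Data collection lists "neurological conditions within 72 h after treatment, complications during hospitalization, follow-up, and presumed reasons of death". Follow-up adds that serious adverse events go to the Institutional Review Board, and sets the poor-outcome range of the modified Rankin Scale at 3 to 6.

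Introduction: a trial of stenting against medical treatment "showed a 14.7% risk of stroke or death in the stenting group versus 5.8% in the medical group at 30 days", and 23% against 15% at a median of 32.4 months.

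**The concern.** When one arm has no procedure and the others do, the main hazard of the procedural arms is concentrated around the intervention and does not respect vascular territory. A stroke endpoint confined to the ipsilateral side captures the benefit the procedure is meant to bring, but only part of the harm it can do.

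The rest of the harm goes into a count of all adverse events for which the article states no grading by severity. That count mixes death and disabling stroke with minor complications and drug effects, so it cannot show which treatment leaves fewer patients dead or with a stroke. A procedural arm could look better on stroke because some of its worst outcomes are classed elsewhere.

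**Working it through.** **Step 1. Where an early event counts.** This sets the definitions in the Abstract, Study endpoints, Follow-up and Discussion side by side. It reads the 6-month endpoint as cumulative and takes a Rankin score of 6 as death, as is conventional.

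| Event soon after treatment | Ipsilateral recurrence | All adverse events | Rankin 3–6 |
|---|---|---|---|
| Ipsilateral stroke, survived | yes | yes | only if disabling at the visit |
| Stroke in another territory, survived | no | yes | only if disabling at the visit |
| Death due to ipsilateral stroke | yes | yes | yes |
| Death from any other cause | no | yes | yes |

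Rows 2 and 4 are the gap. They reach an endpoint only through the unspecific adverse event count or the functional scale.

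**Step 2. When the harm arose in the cited stenting trial.** Inputs are the four Introduction rates for stroke or death.

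- Difference at 30 days: 14.7 − 5.8 = 8.9 percentage points.
- Difference at the median of 32.4 months: 23 − 15 = 8.0 points.
- Increment after 30 days: 23 − 14.7 = 8.3 points (stenting); 15 − 5.8 = 9.2 points (medical).
- Late risk among those event-free at 30 days: 8.3/(100 − 14.7) = 9.7%; 9.2/(100 − 5.8) = 9.8%.
- Share of all events that fell by 30 days: 14.7/23 = 64%; 5.8/15 = 39%.

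The excess arose in the first 30 days and was measured as stroke or death.

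**Step 3. Direction, and why the size stays open.** Suppose a fraction f of the 30-day events were outside an ipsilateral-only endpoint. Take f as equal in both arms and keep all later events. The apparent difference, stenting minus medical, is then

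(8.3 + 14.7(1 − f)) − (9.2 + 5.8(1 − f)) = 8.0 − 8.9f points.

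| f (assumed) | Apparent difference, points |
|---|---|
| 0 | 8.0 |
| 0.5 | 3.55 |
| 1 | −0.9 |

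Any f above zero moves the comparison towards stenting. The Introduction reports stroke or death undivided, so f is unknown and may be small. The f = 1 row is a limit, not a description of this plan. No comparable rates are given for bypass.

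**Step 4. Scale in this trial.** The plan's own figure reproduces only as an inflation, 60 × 1.1 = 66; the base of 60 has no stated derivation. With the Abstract's three arms, 66/3 = 22 per arm. At the cited rates that is 22 × 0.147 = 3.2 against 22 × 0.058 = 1.3 early events. Two-sided power at 0.05 is about 16% for the 30-day rates and about 10% for the long-term rates.

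**The case against.** The strongest case against is that nothing is lost. Death and stroke in any territory are adverse events, and all adverse events is the primary endpoint or part of it. Deaths also enter the poor-outcome range of the Rankin scale. Ipsilateral recurrence is the outcome of the bypass study that the Introduction cites, so it is a recognisable choice. How deaths are handled in the analysis is commonly left to an analysis plan that is not shown.

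This stands as far as it goes: the events are recorded and counted somewhere. It does not answer the point about the stroke endpoint. However the analysis treats deaths, a death from another cause is not an outcome event under the stated definition, and an undifferentiated adverse event count is not a measure of stroke or death.

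A reader might infer four stronger things. The document supports none of them.

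- **That the first month is not assessed, so early events are dropped.** An endpoint at 6 months reads naturally as cumulative, so an early ipsilateral stroke counts. Early complications and reasons for death are also listed for collection.
- **That early events are found unequally by arm.** The 72-hour and in-hospital items have a clearer anchor in a procedural arm than where antithrombotic treatment simply continued. But Data collection limits them to no arm, Study endpoints schedules neurological and imaging examination at 6 months for each patient, and serious adverse events are reported without distinction by arm. An article's silence on interim contacts shows at most a possibility.
- **That moving one or two events would reverse the result because of this endpoint.** The share falling outside is unknown. With power near 16%, the observed direction is fragile under any endpoint, which is a matter of sample size.
- **That the stroke comparison cannot be interpreted.** A bias of known direction and unknown size limits interpretation but does not abolish it.

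**Conclusion.** The point holds as a fault in the endpoint definition. The only stroke-specific endpoint excludes non-ipsilateral strokes, and deaths not due to ipsilateral stroke, around stenting or bypass. It can therefore favour those arms. The size of the bias cannot be derived from the document. The cited figures show only, and for stenting only, that the excess of stroke or death lay in the first 30 days (8.9 points, against 8.3 and 9.2 points accruing later in the two arms).

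This rests on three assumptions: that ipsilateral recurrence means what it says, that the 6-month endpoint is cumulative, and that some procedural deaths or strokes fall outside the ipsilateral territory. If none did, the bias would be zero.

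Separately, and without any assumption, the Abstract and Study endpoints disagree on whether ipsilateral recurrence is primary or secondary.

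**What to change.** In the Abstract and in Study endpoints:

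1. Define the stroke endpoint identically in every arm as any stroke or death from any cause within 30 days, or any ipsilateral stroke after that up to 24 months.
2. Count time from randomization in every arm. At present endpoints run from management and assessments from enrolment, so an event between randomization and a procedure has no clear place. The article gives no interval from randomization to procedure. If some procedures fall late, also describe events within 30 days of the procedure in those arms.
3. Report the 30-day component separately, and keep ipsilateral recurrence as a reported component.
4. Give the endpoint the same primary or secondary status in both places.

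Make the change without sight of outcomes by arm.

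The cost is protocol wording. The endpoint can be built from the adverse event, hospital complication and death data already listed for collection. A 30-day telephone contact in all arms is optional. It means at most 66 calls, by a method Follow-up already allows, and would guard against a possible but undocumented difference in early ascertainment. The small downside is that the composite mixes procedural and later events, which the separate 30-day report addresses.
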